**LIST OF ABBREVIATIONS AND RELEVANT DEFINITIONS**

| **ABR** | **ABR form, General Assessment and Registration form, is the application form that is required for submission to the accredited Ethics Committee** |
| --- | --- |
| **AE** | **Adverse Event** |
| **ANCOVA** | **Analysis of Covariance** |
| **AP** | **Anteroposterior** |
| **AR** | **Adverse Reaction** |
| **ATTL** | **Anterior Talo-Tibial Ligament** |
| **CCMO** | **Central Committee on Research Involving Human Subjects; in Dutch: Centrale Commissie Mensgebonden Onderzoek** |
| **CT** | **Computed Tomography** |
| **CTCM** | **Clinical Trial Center Maastricht** |
| **CV** | **Curriculum Vitae** |
| **DSMB** | **Data Safety Monitoring Board** |
| **GCP** | **Good Clinical Practice** |
| **IC** | **Informed Consent** |
| **METC** | **Medical research ethics committee (MREC); in Dutch: medisch ethische toetsing commissie (METC)** |
| **PTTL** | **Posterior Talo-Tibial Ligament** |
| **ROM** | **Range of Motion** |
| **(S)AE** | **(Serious) Adverse Event** |
| **SE** | **Supination-Eversion** |
| **Sponsor** | **The sponsor is the party that commissions the organisation or performance of the research, for example a pharmaceutical company, academic hospital, scientific organisation or investigator.** |
| **SUSAR** | **Suspected Unexpected Serious Adverse Reaction** |
| **T1** | **First visit at the Zuyderland Medical Center** |
| **T2** | **Second visit at the Zuyderland Medical Center** |
| **T3** | **Third visit at the Zuyderland Medical Center** |
| **Wbp** | **Personal Data Protection Act (in Dutch: Wet Bescherming Persoonsgegevens)** |
| **WMO** | **Medical Research Involving Human Subjects** |
| **X^2^ Test** | **Chi-Squared Test** |

**SUMMARY**

**Rationale:** There is controversy about the optimal conservative treatment of common stable ankle fractures (Weber B or Lauge-Hansen supination-eversion stage 2-4A). The current international guideline describes non-weight bearing and immobilization with a plaster cast for 6 weeks. However, the literature provides no substantiation for this period of non-weight bearing.

Hypothesis 1: We expect earlier functional outcomes in the intervention group than in the control group. Hypothesis 2: We expect the number of complications not to be higher in the intervention group than in the control group. Hypothesis 3: We expect the long-term recovery function (3 months) in the intervention group not to be worse than in the control group. Null hypothesis 1: The treatment in the intervention group is not as effective as the treatment in the control group, because there are worse functional outcomes in the intervention group than in the control group. Null hypothesis 2: The treatment in the intervention group is not as safe as the treatment in the control group, because there are more dislocations of the fractures reported in the intervention group than in the control group.

**Objective**: What are the 6-week and 12-week effects on the functional outcome scores of the ankle in early weight bearing (mobilization with Walker) compared to 6 weeks non-weight bearing and immobilization in conservatively treated stable ankle fractures (Weber B or Lauge Hansen supination-eversion stage 2-4A)?

**Study design:** A prospective randomized controlled trial at the Zuyderland Medical Center . We will include patients at both locations, Heerlen and Sittard/Geleen.

**Study population:** Men and women, 16 years or older, with Weber B ankle fractures treated with a dorsal lower limb cast at the emergency department of both locations of the Zuyderland Medical Center, Heerlen and Sittard/Geleen, The Netherlands.

**Intervention:** One group will get a Walker by which they can start with permissive weight bearing. The other group will get a circular lower limb plaster cast and instructions of non-weight bearing and immobilization till the next visit. After 6 weeks, the Walker or plaster cast will be removed. The patients may then extend the weight bearing to functional.

**Main study parameters/endpoints:** The primary parameter in this study is functional outcome score of the ankle. Secondary parameter is dislocation of the fracture. Other parameters are range of motion of the ankle, circumference of the calf, return to work, satisfaction of the patient and other complications, such as deep vein thrombosis or surgery.

**Nature and extent of the burden and risks associated with participation***,* **benefit an group relatedness:** 3 site visits during 12 weeks with physical examinations and 2 questionnaires which have to be filled in during each visit. Risks of the investigational treatment are myalgia and dislocation of the fracture.

# INTRODUCTION AND RATIONALE

Ankle fractures are among the most common fractures of the lower extremities. With 9% of all fractures, they account for an important part of the traumatic injuries.^1^ A consideration between an operative vs. conservative treatment has to be made. A distinction must be made between stable and unstable ankle fractures.^2^ The fracture is stable if there is a dislocation of less than 3 millimetres at the ‘medial clear space’ (the jointspace between the medial malleolus and the talus) with a symmetrical ankle fork on the Mortise X-ray.

Classifications are used to describe the mechanism behind the ankle fracture and thus to make a statement about the (in)stability of the ankle joint. A common type of injury is the Weber B fracture or according to the Lauge-Hansen classification the supination-eversion type, that can be stable (SE type 2 without rupture of the deltoid ligament) and also possibly unstable (SE type 4 with rupture of the deltoid ligament). This ligament has a superficial and a deep layer. The superficial layer resists plantar flexion and external rotation of the talus relative to the tibia. The deep layer has anterior and posterior components, the anterior and posterior talo-tibial ligaments (ATTL and PTTL), of which the posterior ligament is the strongest. The PTTL is tight when the foot is plantigrade and loose when the foot is plantar flexed. If however, the foot is plantigrade, as on an anteroposterior weight-bearing radiograph, the intact PTTL will prevent lateral translation of the talus and the ankle fork appears congruent.^3^ Therefore, Gougoulias N. et al. (2017) proposed that a (ligamentous) SE type 4 ankle fracture, one without a medial malleolar fracture, with a ruptured superficial and/or ATTL, but an intact PTTL, can be classified as a ‘SE type 4A’ fracture. This is a stable fracture, as long as the foot is in a plantigrade position. With a complete rupture of the superficial and deep components (both ATTL and PTTL) of the deltoid ligament, the medial clear space will open in all positions of the foot, thus also on weight-bearing radiographs. This type of fracture can be classified as SE type 4B, which is always an unstable fracture.

There is controversy about the optimal conservative treatment of common stable ankle fractures. This is confirmed by the presence of a large number of treatment protocols with great variability in weight bearing recommendations.^4^ The current international guideline describes non-weight bearing and immobilization with a plaster cast for 6 weeks.^5^ However, a prolonged period of immobilization causes various negative effects regarding recovery:

- *Patient compliance*: The noncompliance rate with the postoperative weight bearing restriction is almost 30% and they start with weight bearing despite explicit instructions. However, this rarely leads to displacement of the fracture. The advice currently being applied may therefore be too cautious.

# *Physiological cost*: Non-weight bearing with 2 elbow crutches and only 1 leg on the ground costs 4 times more energy than walking with 2 legs on the ground and 2 crutches for support or stabilization.

# *Homeostasis:* Weight bearing ensures the preservation of bone and muscle mass. A few weeks of non-weight bearing results in a significant decrease in bone mass in the affected extremity even a year later.^6^

# *Risk of thrombosis:* Posttraumatic immobilization with a plaster cast is a risk factor for developing a deep venous thrombosis or a pulmonary embolism. At Zuyderland Medical Center, patients receive thromboprophylaxis during long term immobilization, according to protocol.

# Therefore, advising non-weight bearing out of caution or uncertainty can cause harmful effects on the health of patients. However, the literature provides no substantiation for this period of non-weightbearing.^7^ When transmitting anxiety to patients, this can make them insecure, which does not contribute to rehabilitation.

# Previous findings: According to our knowledge, there has not been previously performed a prospective randomized comparative study on early weight bearing in conservatively treated stable ankle fractures (Weber B of Lauge Hansen SE2-4A). Van Laarhoven^8^ refers in his thesis to two studies^9,10^ in which early weight bearing of stable Weber B fractures yields good to excellent functional results. However, both studies have a limited size of the study population and control groups are lacking.

# Relevance: According to an epidemiological study of Court-Brown et. Al, Weber B ankle fractures (Lauge Hansen SE2) with 21% have the highest incidence within the total number of ankle fractures (n=1500).^11^ According to the current trend, more and more rehabilitation programs use early weight bearing. However, this does not apply to this large group of patients if the current protocols continue to be used. If our hypotheses are correct, old recommendations about long term immobilization could be abandoned and we can opt for a more patient-oriented follow-up treatment.

# OBJECTIVES

**Objective:** What are the 6-week and 12-week effects on the functional outcome scores of the ankle in early weight bearing (mobilization with Walker) compared to 6 weeks non-weight bearing and immobilization in conservatively treated stable ankle fractures (Weber B or Lauge Hansen supination-eversion stage 2-4A)?

**Secondary Objective:** What is the 6-week effect on dislocation of the fracture in early weight bearing (mobilization with Walker) compared to 6 weeks non-weight bearing and immobilization in conservatively treated stable ankle fractures (Weber B or Lauge Hansen supination-eversion stage 2-4A)?

**Other Objectives:** Other outcome measures include range of motion (ROM) of the ankle circumference of the calf, return to work, mental health outcome scores and rates of other complications.

**Hypothesis 1:** We expect earlier functional outcomes in the intervention group than in the control group.

**Hypothesis 2:** We expect the number of complications not to be higher in the intervention group than in the control group.

**Hypothesis 3:** We expect the long-term recovery function (3 months) in the intervention group not to be worse than in the control group.

**Null hypothesis 1**: The treatment in the intervention group is not as effective as the treatment in the control group, because there are worse functional outcomes in the intervention group than in the control group.

**Null hypothesis 2:** The treatment in the intervention group is not as safe as the treatment in the control group, because there are more dislocations of the fractures reported in the intervention group than in the control group.

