**Follow-up**

The patients will visit the traumatology department after 6 weeks ***(= t2)*** and 12 weeks ***(= t3)*** posttraumatic. During the visit after 6 weeks, radiographs of the ankle joint are obtained at 3 different views (anteroposterior (AP), lateral and Mortise). Furthermore, they will undergo a comprehensive examination that will include assessment of ankle dorsal flexion/ plantar flexion with use of a goniometer. The circumference of the calf will be measured with a tapeline. This will be performed by the trained research staff or by doctors trained and instructed by them.

Each visit ***(t1, t2 ánd t3)*** the patients receive 2 questionnaires with regard to return to work or sport, daily activities and limiting factors.

[figure not shown]

Figure 1. Flowchart

[figure not shown]

Figure 2. Timeline

| Variable (outcome measure) | Type | t1 | t2 | t3 | Total |
| --- | --- | --- | --- | --- | --- |
| Functional outcome score (OMAS, 0-100) | continuous | ✓ | ✓ | ✓ | 3 |
| Dislocation of the fracture (Yes/No) | binary | ✓ | ✓ | × | 2 |
| Range of motion of the ankle (degrees) | continuous | ✓ | ✓ | ✓ | 3 |
| Circumference of the calf (cm) | continuous | ✓ | ✓ | ✓ | 3 |
| Return to work (%) | continuous | ✓ | ✓ | ✓ | 3 |
| Satisfaction (SF-36, 0-100) | continuous | ✓ | ✓ | ✓ | 3 |
| Other complications | nominal | × | ✓ | ✓ | 2 |

Table 1. Measurements

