# METHODS

## Study parameters/endpoints

### Main study parameter/endpoint

Functional outcome scores of the ankle. This will be indicated with the Olerud/Molander Ankle Function Score (OMAS). This is a continuous variable (0-100 points).

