## Primary study parameter(s)

The continuous variables will be presented as quantitative variables. The ANCOVA will be used to adjust for baseline values. A P-value of less than 0.05 was considered statistically significant. Patients were analysed based on per protocol principles.

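### The primary objective names OMAS at both 6 and 12 weeks without fixing a primary visit, and a difference test without a margin cannot support the 12-week not-worse hypothesis when it is non-significant

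*Protocol*

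**What the plan says.** The main objective (Protocol, section 2 Objectives, repeated in the Summary) asks "What are the 6-week and 12-week effects on the functional outcome scores of the ankle in early weight bearing" compared with six weeks of non-weight bearing. The two time points are not ranked.

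The same section gives them different hypotheses. Hypothesis 1 reads "We expect earlier functional outcomes in the intervention group than in the control group". Hypothesis 3 reads "We expect the long-term recovery function (3 months) in the intervention group not to be worse than in the control group". Null hypothesis 1 reads "The treatment in the intervention group is not as effective as the treatment in the control group, because there are worse functional outcomes" than under control; it has no margin and no time point.

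The sections that should settle the matter do not:
- Section 8.1.1 (main endpoint) defines the endpoint as the OMAS, a continuous 0–100 score, with no visit.
- Table 1 in section 3 schedules the OMAS at t1, t2 (6 weeks) and t3 (12 weeks).
- Section 4.4 (sample size) gives 23 per group for 80% power at 0.05. It takes means and SDs from a cited post-operative trial without reporting them or naming a visit.
- Section 10.1 (primary analysis) specifies a baseline-adjusted ANCOVA and "A P-value of less than 0.05 was considered statistically significant". It gives no visit, test order, split of alpha or margin.

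**The concern.** There are two linked problems.

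**No primary visit.** With two unranked visits in one primary objective and one threshold, the reader cannot tell which comparison decides the trial. The choice could be made after the data are seen. The sample size is affected too, because the expected OMAS difference and SD may differ between 6 and 12 weeks.

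**Hypotheses and test do not match.** Hypothesis 1 is a superiority claim. Hypothesis 3 is a non-inferiority claim, and null hypothesis 1 is worded as inferiority. The ordinary null of an ANCOVA is no difference. Failing to reject that null does not show that the intervention is not worse; it may only show that the trial is small.

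The introduction says that if the hypotheses are correct, long-term immobilisation advice could be abandoned. An unsupported not-worse conclusion at 12 weeks would therefore bear directly on practice.

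**Working it through.** **Inputs.** From the protocol: 23 per group, 80% power, alpha 0.05 (section 4.4); ANCOVA with P<0.05 (section 10.1). Assumed, because the protocol does not give them: two-sided tests, the correlation r between the 6- and 12-week test statistics, the baseline–outcome correlation ρ, the size of a 12-week deficit, and any margin. Effects are in SD units because no SD is given.

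**1. The plan's own figure.** The 23 per group cannot be reproduced, because no difference or SD is stated. Solved backwards by the normal approximation, the implied effect is (1.960 + 0.842) × √(2/23) = 0.826 SD. Nothing shows which visit this effect belongs to.

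**2. Two visits at 0.05, if either one counted.** Two-sided: P(|Z₁|>1.96 or |Z₂|>1.96), with Z₁ and Z₂ bivariate normal. In the intervention's favour: P(Z₁>1.96 or Z₂>1.96).

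| r (assumed) | Any false positive, two-sided | In the intervention's favour |
|---|---|---|
| 0.3 | 9.5% | 4.8% |
| 0.5 | 9.1% | 4.5% |
| 0.7 | 8.3% | 4.2% |
| 0.9 | 7.0% | 3.5% |
| Nominal, one test | 5% | 2.5% |

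If significance were required at both visits, the false-positive rate could not exceed the nominal one.

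**3. What a non-significant 12-week result can exclude.** The 95% CI half-width is t × √(2/23) × √(1−ρ²) SD. A true deficit δ is non-significant with probability P(|T|≤t), where T is noncentral t with noncentrality δ√(23/2)/√(1−ρ²). Take δ = 0.5 SD.

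- No adjustment, 44 df: 2.0154 × 0.2949 = 0.594 SD. Probability of non-significance 61.8%.
- ρ = 0.3, 43 df: 2.0167 × 0.2949 × 0.954 = 0.57 SD. Probability 59%.
- ρ = 0.5, 43 df: 2.0167 × 0.2949 × 0.866 = 0.52 SD. Probability 52%.

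A trial with an observed 12-week difference of exactly zero would thus still be compatible with a deficit of about half an SD.

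**4. Power if a margin were added.** Test at one-sided 0.025, true difference zero, no baseline adjustment, normal approximation: power = Φ(M√(23/2) − 1.96).

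- M = 0.5 SD: Φ(1.696 − 1.960) = Φ(−0.264) = 40%. For 80% power, n = 2 × (1.960 + 0.842)²/0.5² = 62.8, so 63 per group.
- M = 0.75 SD: Φ(2.543 − 1.960) = Φ(0.583) = 72%. For 80% power, n = 27.9, so 28 per group.

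**The case against.** **The visits have different roles.** Hypothesis 1 speaks of earlier recovery and Hypothesis 3 of 3 months. On that reading there is one early superiority claim and one late reassurance claim, not two interchangeable routes to success. This largely stands. A reader might infer that a positive result at either visit counts as success, but the protocol has no success rule, so the error-rate figures are conditional. The objection does not remove the gap, because sections 4.4, 8.1.1 and 10.1 never assign a hypothesis to a visit.

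**The two-sided figure overstates the risk.** About half of it is false positives favouring control. This stands: the more relevant range is 3.5–4.8% against 2.5%.

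**Hypothesis 3 is not untestable.** A reader might infer that the plan offers no valid test of it at all. That goes too far. A significant 12-week benefit would support not worse, and the ANCOVA yields an interval that can be read. Nor does the protocol say that a non-significant P-value will be reported as not worse. What remains is that a non-significant result cannot support the claim and that no margin is stated against which to judge the interval.

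**The unadjusted figures are pessimistic.** They are; baseline adjustment narrows the interval. The range above allows for this and the conclusion is unchanged.

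**A statistical analysis plan may say more.** Detailed multiplicity rules may well sit there. But the protocol itself puts two visits in its primary objective and states a not-worse hypothesis, and its sample size depends on which comparison is meant.

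**Conclusion.** The point holds in two parts. First, the primary objective names two visits and the endpoint, sample size and primary analysis choose neither. The possible cost in error rate is modest and conditional: it arises only if either visit may count, and its size rests on assumed correlations of 0.9 to 0.3.

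Second, the not-worse hypothesis at 12 weeks and the inferiority wording of null hypothesis 1 do not match a difference test without a margin. This part is firmer. It rests on 23 analysed per group, an assumed 0.5 SD deficit and an assumed baseline correlation of 0 to 0.5, and more often than not such a deficit would go undetected.

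The protocol should be changed. Confidence is high on the missing visit and the mismatch, and medium on the error-rate inflation.

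**What to change.** - **Primary visit.** In sections 4.4, 8.1.1 and 10.1, name one OMAS visit as primary, with a two-sided superiority test at 0.05 and a null of no difference. Six weeks fits Hypothesis 1, but the choice is the sponsor's, who should bear in mind that controls have their cast removed at that same visit.
- **Null hypothesis 1.** Reword it to match that test.
- **Sample size.** Confirm that 23 per group was derived for the chosen visit, and give the means and SD used. They may already be the right ones; the text does not show it.
- **Other visit.** Make it secondary.
- **Hypothesis 3.** Claim not worse at 12 weeks only if the 95% confidence limit excludes a margin justified in advance. Otherwise report the difference and its confidence interval without that claim. State that a non-significant P-value will not be read as not worse.

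**Cost.** Naming the visit is a wording change and, if the 23 was derived for it, leaves alpha and sample size alone. If 6 weeks is chosen, the 12-week result is no longer a stand-alone primary success. The non-inferiority claim costs more than wording: it needs a justified margin, and its low power at 23 per group (about 40% for an assumed 0.5 SD margin, unadjusted) should be stated. If the sponsor wants that claim to be properly powered, the sample size must rise; if not, reporting the interval alone costs nothing.

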# STUDY DESIGN

A prospective randomized controlled trial at the Zuyderland Medical Center. We will include patients at both locations, Heerlen and Sittard/Geleen.

All patients with ankle fractures at the emergency department of both locations of the Zuyderland Medical Center are treated with a dorsal lower limb cast. 7 to 10 days posttraumatic, they are seen again at the traumatology department, according to protocol.

During this visit ***(= t1)****,* radiographs of the ankle joint are obtained at 3 different views (anteroposterior (AP), lateral and Mortise) and a weight-bearing radiograph (AP). When it’s a stable fracture according to the surgeon, present at that time, the patients will be approached to participate in this randomized study. If written informed consent is obtained, the patients get included.

**Intervention group**

The dorsal lower limb cast will be removed by the plaster technician. Patients will get a Walker by which they can start with permissive weight bearing. According to protocol, they receive daily thromboprophylaxis (Fragmin 5000IE s.c.). After 6 weeks posttraumatic, the Walker will be removed at the traumatology department. The patients may then extend the weight bearing to functional.

**Control group**

The dorsal lower limb cast will be removed by the plaster technician and a circular lower limb plaster cast will be applied. Patients get explicit instruction of non-weight bearing and immobilization till the next visit. According to protocol, they receive daily thromboprophylaxis (Fragmin 5000IE s.c.). After 6 weeks posttraumatic, the plaster cast will be removed at the traumatology department. The patients may then start weight bearing to their own abilities.

**Follow-up**

The patients will visit the traumatology department after 6 weeks ***(= t2)*** and 12 weeks ***(= t3)*** posttraumatic. During the visit after 6 weeks, radiographs of the ankle joint are obtained at 3 different views (anteroposterior (AP), lateral and Mortise). Furthermore, they will undergo a comprehensive examination that will include assessment of ankle dorsal flexion/ plantar flexion with use of a goniometer. The circumference of the calf will be measured with a tapeline. This will be performed by the trained research staff or by doctors trained and instructed by them.

Each visit ***(t1, t2 ánd t3)*** the patients receive 2 questionnaires with regard to return to work or sport, daily activities and limiting factors.

[figure not shown]

Figure 1. Flowchart

[figure not shown]

Figure 2. Timeline

| Variable (outcome measure) | Type | t1 | t2 | t3 | Total |
| --- | --- | --- | --- | --- | --- |
| Functional outcome score (OMAS, 0-100) | continuous | ✓ | ✓ | ✓ | 3 |
| Dislocation of the fracture (Yes/No) | binary | ✓ | ✓ | × | 2 |
| Range of motion of the ankle (degrees) | continuous | ✓ | ✓ | ✓ | 3 |
| Circumference of the calf (cm) | continuous | ✓ | ✓ | ✓ | 3 |
| Return to work (%) | continuous | ✓ | ✓ | ✓ | 3 |
| Satisfaction (SF-36, 0-100) | continuous | ✓ | ✓ | ✓ | 3 |
| Other complications | nominal | × | ✓ | ✓ | 2 |

Table 1. Measurements

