# STUDY POPULATION

## Population (base) Men and women with a Weber B or isolated malleolus tertius ankle fracture treated with a dorsal lower limb cast at the emergency department of both locations of the Zuyderland Medical Center, Heerlen and Sittard/Geleen, The Netherlands.

## Inclusion criteria

In order to be eligible to participate in this study, a subject must meet all of the following criteria:

- Age of 16 years and older.
- Stable ankle fracture (non-dislocated Weber B or Lauge Hansen supination-eversion stage 2-4A fracture, isolated malleolus tertius fracture).
- Conservative treatment with a dorsal lower limb cast.

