## Other study parameters

The continuous variables will be presented as quantitative variables. The ANCOVA will be used to adjust for baseline values. The X^2^ test will be used for nominal variables. A P-value of less than 0.05 was considered statistically significant. Patients were analysed based on per protocol principles.

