## Benefits and risks assessment, group relatedness

Benefits of the investigational treatment can be an earlier return to work or sport. Risks of the investigational treatment are myalgia and dislocation of the fracture. We expect the the latter to occur rarely, if ever.

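### Return to work is a percentage at three visits, with no pre-injury work status and no date of return, so the trial cannot estimate how much earlier patients return

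*Protocol*

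**What the plan says.** - **Measure.** Section 3, Table 1 has the row "Return to work (%) | continuous | ✓ | ✓ | ✓ | 3". The protocol does not say what the percentage is a share of (hours, duties or patients).
- **Source.** Under Follow-up in section 3, at each visit "the patients receive 2 questionnaires with regard to return to work or sport, daily activities and limiting factors". Section 8.3 names these as the OMAS and the RAND 36-item survey. No separate work form and no date of return is mentioned.
- **Timing.** Before t1, "All patients with ankle fractures at the emergency department of both locations of the Zuyderland Medical Center are treated with a dorsal lower limb cast". For t1 itself, "7 to 10 days posttraumatic, they are seen again at the traumatology department, according to protocol". The later visits are at 6 weeks ("The patients will visit the traumatology department after 6 weeks") and at 12 weeks.
- **Analysis.** Section 10.3, for the other continuous parameters: "The ANCOVA will be used to adjust for baseline values".
- **Population.** Section 4.2 sets "Age of 16 years and older". Sections 4.2 and 4.3 contain no upper age limit and no employment condition.
- **Baseline and stratification variables.** Section 10 lists gender, age, quality of life, smoking status and diabetes as baseline values. Section 8.2 stratifies by gender, age, smoking status and diabetes. Work before the injury is in neither list.
- **Purpose.** Section 11.4: "Benefits of the investigational treatment can be an earlier return to work or sport". Return to work is an 'other' parameter (section 8.1.3) and appears in none of the hypotheses in section 2.

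**The concern.** The benefit in section 11.4 concerns timing, but the planned measure records a level at fixed visits. After t1 there are two looks, six weeks apart, so a return between weeks 6 and 12 shows only as work resumed by week 12.

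The t1 value does not supply the missing reference. A worker on sick leave and a retired person can both score zero a week after the fracture, so adjusting for t1 does not separate them. With entry from age 16 and no upper limit, some patients will probably be students, retired or unemployed. Because pre-injury work is not listed as a baseline variable, the rule in section 10 for adding imbalanced baseline variables to the model could not act on it.

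At stake are the interpretability of this one parameter and some of its power. An SAP could later define a denominator or an analysis set, but it cannot recover pre-injury work status or return dates that were never collected.

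**Working it through.** The protocol gives no effect, SD or sample size for return to work, so there is no figure of its own to reproduce. The inputs marked 'assumed' below are illustrative.

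**1. Dilution.** Let q be the share not working before injury, m0 and m1 the mean percentages among workers in the two arms, and c any fixed score given to non-workers in both arms.

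Difference over all patients = [(1 − q)·m1 + q·c] − [(1 − q)·m0 + q·c] = (1 − q)·(m1 − m0).

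The score c cancels. With q assumed at 0.20 to 0.40, the difference shrinks by 20% to 40%.

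**2. Effect on power.** Inputs: 23 per arm (section 4.4, calculated there for the OMAS); two-sided 0.05 (the protocol does not state sidedness); among workers, assumed SD 40 and means 30 and 63. The worker effect is set at the standardised difference that 23 per arm detects with 80% power: (1.960 + 0.842) × √(2/23) = 0.826, and 0.826 × 40 = 33 points. No gain from adjusting for t1 is assumed.

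| Share employed | All patients, non-workers coded 0 | All patients, non-workers coded 100 | Workers only |
|---|---|---|---|
| 100% | 80% | 80% | 80% |
| 80% | 59% | 57% | 71% |
| 60% | 40% | 37% | 58% |
| 40% | 25% | 22% | 43% |

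Example at 60% employed, coded 0: the difference is 0.6 × 33.0 = 19.8 and the SD of the mixture is 39.3. Then 19.8 / (39.3 × √(2/23)) = 1.71, and 1.71 − 1.96 = −0.25, which gives 40%. Restricting to workers recovers part of the loss. The rest comes from having fewer informative patients and cannot be recovered.

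**3. Chance imbalance in employment.** Take 25 per arm (half of the stated total of 50), with an assumed 30% not working and a worker mean of 50. The SD of the between-arm difference in the non-working share is √(2 × 0.3 × 0.7 / 25) = 0.130, or 0.130 × 50 = 6.5 points on the outcome. This is already part of the standard error. With SD 40, the standard error for 25 workers per arm is 40 × √(2/25) = 11.3. With 30% coded 0, the variance is 0.7 × 1600 + 0.3 × 0.7 × 2500 = 1645, and the standard error is √(1645 × 2/25) = 11.5. Imbalance adds almost nothing to the error; the damage is the smaller difference in step 1.

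**4. Snapshot against dated return.** Assumed: exponential times to return starting at about week 1.2, hazard ratio 2, control median 4 to 8 weeks, 23 per arm. Each snapshot is treated as a comparison of proportions returned; dated return uses the Schoenfeld formula with follow-up to week 12.

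| Share employed | Week-6 snapshot | Week-12 snapshot | Time to return |
|---|---|---|---|
| 100% | 33–43% | 34–44% | 52–61% |
| 60% (workers only) | 21–28% | 22–28% | 34–41% |

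Example, all employed, median 6 weeks: the proportions returned by week 12 are 0.71 and 0.92, giving about 23 × 1.63 = 37.5 events. Then √(37.5/4) × ln 2 = 2.12, and 2.12 − 1.96 = 0.16, which gives 56%. The week-6 snapshot (0.43 against 0.67) has 38%.

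A snapshot is weaker but not empty. What it cannot give is a time or a difference in time.

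**The case against.** The best case for the protocol is that much of this is detail left to an SAP or case report form. Nothing says that patients without a job are scored, or scored as zero. A return-to-work percentage may presuppose prior work and simply not apply to a retired person. The endpoint ranks below primary and secondary, and no sample size rests on it. This stands, and it limits the severity. It does not answer the missing data items: if the forms already collect pre-injury work and return dates, the protocol gives no sign of it, and its planned analysis does not use them.

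A reader might infer three stronger points, none of which the protocol supports:

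- **That the trial cannot show earlier return at all.** The assigned devices are worn until 6 weeks, which is when t2 falls. More work resumed at week 6 in one arm would be indirect evidence of earlier return.
- **That non-workers bias the comparison.** Randomisation balances employment in expectation, and step 3 shows that chance imbalance is ordinary sampling error. Only dilution remains, and only if non-workers receive a fixed score. (The per-protocol analysis set is a separate matter.)
- **That the t1 OMAS is an invalid baseline, or that Hypothesis 3 lacks a reference.** Hypothesis 3 compares the two arms and needs no pre-injury value. The t1 visit comes before the allocated device is worn, so it is a legitimate baseline. A weak covariate costs precision, not validity.

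**Conclusion.** The point holds in a limited form. As planned, return to work supports a comparison of the level resumed at 6 and 12 weeks. It does not support an estimate of how much earlier patients return, and t1 cannot identify who had work to return to.

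The size depends on facts the protocol does not give. If 20–40% of patients are not working and are kept at a fixed score, the mean difference falls by 20–40%. On the assumptions in step 2, with non-workers coded 0, power falls from 80% to 59–40%, against 71–58% in workers only. At an assumed hazard ratio of 2 with everyone employed, dated return gives 52–61% power, against 33–44% for a single snapshot. Under any of these analyses the parameter remains exploratory at this sample size.

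Severity is minor: this is a cheap improvement to an 'other' parameter, and it leaves the primary analysis untouched.

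**What to change.** - At t1, before randomisation, record work before the injury (yes/no, hours) and sport before the injury, and add work status to the baseline table.
- At t2 and t3, record the dates of first partial and first full return to work and to sport.
- Replace the ANCOVA on the t1 percentage with an analysis of time to return, censored at t3, among patients who worked before the injury. State the time origin and how patients already back at work at t1 are handled.
- If the percentage is kept as a description of weeks 6 and 12, define what it is a share of and report it for pre-injury workers only.

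The cost is a few questions at existing visits and one changed analysis, with no added visit. The downsides are some recall error, which should not differ by arm for items collected before randomisation but could for dates reported later in an unblinded trial, and a smaller denominator. If the case report form already holds these items, only the protocol text and the analysis need to change.
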